## Abstract

**Background:**

Chronic fatigue syndrome (CFS) is a disabling multisystem disorder characterized by persistent fatigue, post-exertional malaise, unrefreshing sleep, and neurocognitive and gastrointestinal symptoms. Effective non-pharmacological treatments remain limited. Increasing evidence suggests that CFS involves not only peripheral metabolic and gastrointestinal abnormalities but also central nervous system dysfunction. Altered tryptophan metabolism and gut-brain axis dysfunction may contribute to its pathophysiology. Tuina, a manual therapy used in traditional Chinese medicine, has been hypothesized to influence somatosensory, autonomic, stress-related, and gastrointestinal pathways. However, randomized controlled trials evaluating its clinical effects and exploratory gut-brain correlates in CFS remain scarce.

**Methods:**

This multicenter, parallel-group, randomized controlled trial will enroll 166 participants with CFS, who will be allocated in a 1:1 ratio to a Tuina group or a standardized usual care group. The Tuina group will receive treatment twice weekly for 8 weeks, whereas the control group will receive standardized usual care consisting of health education and symptom-oriented management. The primary objective is to evaluate the effectiveness of Tuina on fatigue severity, assessed by the change in Fatigue Scale-14 (FS-14) score from baseline to week 8. Secondary outcomes include quality of life, sleep, pain, anxiety, depression, gastrointestinal symptoms, bowel function, and handgrip strength. Exploratory mechanistic outcomes include plasma tryptophan-pathway metabolites, gut microbiota profiling, resting-state functional magnetic resonance imaging, and magnetic resonance spectroscopy. Assessments will be conducted at baseline, weeks 4 and 8, and at 12 and 24 weeks after completion of treatment.

**Discussion:**

This study is designed to evaluate the clinical effects of Tuina in CFS while exploring a biologically informed gut-brain framework involving tryptophan metabolism, gut microbiota, and brain network alterations. To our knowledge, few randomized trials in CFS have prospectively integrated clinical, metabolomic, microbiome, and multimodal neuroimaging measures within a single protocol. The findings may help clarify whether a non-pharmacological intervention can modulate interconnected peripheral and central pathways relevant to fatigue and related symptoms.

**Clinical trial registration:**

https://itmctr.ccebtcm.org.cn/mgt/project/view/1990257056896122880, Identifier ITMCTR2025002204.

## Introduction

1

CFS is a complex multisystem disorder characterized by persistent disabling fatigue, post-exertional malaise, unrefreshing sleep, and a range of neurocognitive and gastrointestinal symptoms (National Institute for Health and Care Excellence (NICE), 2021). The global prevalence varies by case definition and study design, roughly 0.1–0.8% or up to around 1% (Vester et al., 2026). These manifestations substantially impair daily functioning and quality of life and impose a considerable social and economic burden. Current management is largely supportive, and some activity-based approaches may be poorly tolerated by patients who are prone to post-exertional symptom exacerbation. These considerations have renewed interest in low-burden, symptom-oriented interventions.

Although research on CFS has expanded in recent years, its pathophysiology remains insufficiently understood. Recent work increasingly supports a multisystem model of CFS involving peripheral metabolic, gastrointestinal, and central nervous system abnormalities. The 2021 NICE guideline no longer recommends graded exercise therapy based on fixed incremental increases in activity as a treatment for CFS, and it positions cognitive behavioral therapy as a supportive intervention to help patients manage symptoms rather than as a curative treatment (National Institute for Health and Care Excellence (NICE), 2021). In routine practice, symptomatic management is one of the main clinical approaches, yet many patients show little improvement in fatigue or post-exertional malaise even when care is consistent with current guidelines (Larun et al., 2024). In addition, activity-based interventions may be unsuitable for individuals who are prone to post-exertional symptom exacerbation. These limitations highlight the need to evaluate safe complementary and alternative therapies that may relieve symptoms and support physiological recovery in CFS. Patients commonly present with cognitive disturbance, pain sensitivity, autonomic dysregulation, and affective symptoms, and neuroimaging studies have reported altered functional connectivity across distributed large-scale brain networks in CFS (Inderyas et al., 2024). At the same time, growing evidence implicates gut microbial dysbiosis, altered microbial metabolites, and disturbed tryptophan-related pathways in symptom generation and persistence. These observations support the view that CFS involves abnormalities in distributed large-scale brain networks.

Non-pharmacological approaches are receiving increasing attention in CFS because some low-burden, symptom-oriented interventions may be more acceptable for patients with post-exertional malaise (PEM) (Wang et al., 2023; Li et al., 2024). Tuina is a structured manual therapy that delivers controlled tactile and pressure stimulation to defined body regions and acupoints (Ma et al., 2023). Preliminary studies suggest that Tuina may alleviate fatigue and improve gastrointestinal symptoms in patients with CFS (Li et al., 2017; Dai et al., 2023). More broadly, Tuina may exert multisystem effects through peripheral somatosensory stimulation, with potential downstream influences on autonomic regulation, stress responses, and gut-related function. Beyond its musculoskeletal effects, it may also enhance parasympathetic activity, modulate hypothalamic–pituitary–adrenal axis responses, and influence gastrointestinal motility (Geng et al., 2020; Packheiser et al., 2024).

At the same time, gastrointestinal symptoms are common in CFS, and growing evidence suggests that gut microbial composition, microbial metabolites, barrier-related processes, and immune signaling may be altered in this population (El-Sehrawy et al., 2025). In parallel, manual therapy applied to the abdomen and adjacent regions has been proposed to influence gastrointestinal motility and related visceral function, while other manual therapy studies suggest that such interventions may also modulate autonomic activity, including vagal responses (Goldenberg and Kalichman, 2024; Henley et al., 2008). Taken together, these observations raise the possibility that Tuina could affect gut-related physiological processes relevant to the gut-brain axis, including tryptophan metabolism, although these mechanisms remain to be clarified (Groven et al., 2021; König et al., 2022). However, rigorous randomized trials evaluating Tuina as an intervention for CFS remain scarce, and the mechanistic links among tryptophan metabolism, gut microbiota composition, and brain network function are still poorly defined. Importantly, these central abnormalities may not be independent of peripheral biological disturbances, particularly those involving immune signaling, gut microbial metabolism, and neuroactive metabolic pathways. In this context, tryptophan metabolism may provide a biologically plausible link between gut microbial alterations and central nervous system dysfunction, because tryptophan-derived metabolites can influence immune signaling, neuroactive pathways, and brain function. Therefore, an integrative design combining metabolomic, microbiome, and neuroimaging measures may help clarify whether peripheral and central abnormalities in CFS are mechanistically connected. Within this framework, tryptophan metabolism is considered a potential biological interface connecting gut microbiota-related alterations with central nervous system functional changes. Accordingly, microbiome and neuroimaging assessments are incorporated as complementary approaches to contextualize peripheral and central biological responses associated with clinical improvement following Tuina intervention.

In summary, Tuina may represent a low-risk and adaptable option for CFS, but its therapeutic effects and underlying mechanisms remain insufficiently characterized. This trial is designed to evaluate the efficacy of Tuina for reducing fatigue and improving related symptoms in patients with CFS. Gastrointestinal symptoms will be assessed as an important clinical and mechanistic domain rather than as an entry criterion. In addition, multimodal assessments, including functional MRI, magnetic resonance spectroscopy, metabolomic analysis, and metagenomic profiling, will be used to explore potential gut-brain mechanisms, with particular attention to associations among gut microbial features, tryptophan-related metabolites, and brain functional characteristics in CFS.

## Objectives and hypotheses

2

### Primary objective

2.1

To evaluate the effectiveness of Tuina versus standardized usual care in reducing fatigue severity in patients with chronic fatigue syndrome, based on the change in FS-14 total score from baseline to week 8.

### Secondary clinical objectives

2.2

To assess the effects of Tuina on quality of life, sleep, pain, emotional symptoms, gastrointestinal symptoms, bowel function, and handgrip strength.

### Exploratory mechanistic objective

2.3

To explore whether clinical improvement is accompanied by changes in tryptophan-pathway metabolites, gut microbiota composition, and brain functional and neurochemical measures, thereby generating hypotheses regarding potential gut-brain mechanisms of Tuina in CFS.

### Hypotheses

2.4

We hypothesize that, compared with standardized usual care, Tuina will produce greater improvement in fatigue severity and related clinical outcomes in patients with CFS. We further hypothesize that these clinical changes may be accompanied by alterations in tryptophan-pathway metabolites, gut microbiota composition, and brain functional or neurochemical measures, consistent with a modulating effect on gut-brain mechanisms relevant to CFS.

## Methods and analysis

3

### Study design

3.1

This study is a multicenter, parallel-group, open-label randomized controlled trial with blinded outcome assessors and statisticians. The trial is organized with Shuguang Hospital Affiliated to Shanghai University of Traditional Chinese Medicine serving as the primary study center and Yueyang Hospital of Integrated Traditional Chinese and Western Medicine participating as an additional recruiting center. The study protocol has been approved by the Ethics Committee of Shuguang Hospital Affiliated to Shanghai University of Traditional Chinese Medicine and by the Ethics Committee of Yueyang Hospital of Integrated Traditional Chinese and Western Medicine, and has been registered at the International Traditional Medicine Clinical Trial Registry (ITMCTR2025002204). Participants will be randomly allocated in a 1:1 ratio to either the Tuina group or the control group (standardized usual care), and both groups will receive their assigned interventions for 8 weeks. Outcome assessments will be conducted at baseline, week 4, week 8 (end of treatment), and 12 and 24 weeks after the end of treatment. To improve participant retention and acknowledge trial participation, participants in the control group will be offered two Tuina sessions after completion of the final 24-week follow-up assessment. This protocol was developed in accordance with the Standard Protocol Items: Recommendations for Interventional Trials (SPIRIT) statement (Chan et al., 2025). The study flowchart is presented in Figure 1, and the detailed schedule of enrollment, interventions, and assessments is shown in Table 1.

**Figure 1 fig1:**
[figure not shown]
The flow chart of this trial.

**Table 1 tab1:** Study schedule.

Time points	Study period					
	Enrollment	Treatment			Follow-up	
	Week −1	Week 0	Week 4	Week 8	12 weeks post-treatment	24 weeks post-treatment
Enrollment						
Eligibility screen	✓					
Informed consent	✓					
Demographic characteristics	✓					
Medical history	✓					
Allocation		✓				
Physical Examination	✓					
Comorbidities	✓					
Interventions						
Tuina		✓	✓	✓		
Standardized usual care		✓	✓	✓		
Outcomes						
FS-14		✓	✓	✓	✓	✓
SF-36		✓	✓	✓	✓	✓
Pain-VAS		✓	✓	✓	✓	✓
PSQI		✓	✓	✓	✓	✓
SAS		✓	✓	✓	✓	✓
SDS		✓	✓	✓	✓	✓
GSRS		✓	✓	✓	✓	✓
BSFS		✓	✓	✓	✓	✓
HGS		✓	✓	✓	✓	✓
fMRI		✓		✓		
MRS		✓		✓		
Blood and fecal metabolites		✓		✓		
Metagenomic Sequencing		✓		✓		
Assessments						
Patient compliance		✓	✓	✓		
Adverse events		✓	✓	✓		
Concomitant medications		✓	✓	✓	✓	✓

FS-14, Fatigue Scale-14; SF-36, 36-Item Short Form Health Survey; Pain-VAS, Visual Analog Scale of Pain; PSQI, Pittsburgh Sleep Quality Index; SAS, Self-Rating Anxiety Scale; SDS, Self-Rating Depression Scale; GSRS, Gastrointestinal Symptom Rating Scale; BSFS, Bristol Stool Form Scale; HGS, Handgrip strength; fMRI, functional Magnetic Resonance Imaging; MRS, Magnetic Resonance Spectroscopy; Weeks 0, 4, and 8 are counted from baseline; week 8 corresponds to the end-of-treatment assessment. Follow-up assessments are scheduled at 12 and 24 weeks after completion of treatment.

### Participant recruitment

3.2

Participants for the randomized trial will be recruited through Shuguang Hospital Affiliated to Shanghai University of Traditional Chinese Medicine and Yueyang Hospital of Integrated Traditional Chinese and Western Medicine. Recruitment strategies will include posting study notices on the hospital website and official WeChat account, displaying posters and flyers in outpatient waiting areas and community locations, and disseminating study information through WeChat outreach. Interested individuals may complete an initial prescreening questionnaire by telephone or via a secure WeChat form, including self-reported symptoms, medical history, and basic demographic information. This remote prescreening process is intended to facilitate participation for individuals with transportation constraints.

Individuals who appear to meet the preliminary eligibility criteria will be invited to an on-site screening visit at the participating center at which they are recruited. At this visit, a designated study physician will provide the participant information sheet, obtain written informed consent, and assess eligibility. Participants who meet all eligibility criteria will then complete the baseline assessment and proceed to randomization. A screening log will be maintained to document all contacts, eligibility decisions, and reasons for exclusion. During screening, alternative clinical explanations for fatigue, including post-COVID condition when clinically relevant, will be considered by the study physician in determining trial eligibility.

### Eligibility criteria

3.3

Inclusion criteria:

1) The diagnostic criteria of potential participants refer to the 2015 Institute of Medicine (IOM) criteria for CFS (Clayton, 2015):

Substantial reduction or impairment in activity level with fatigue >6 months,Post-exertional malaise (PEM),Unrefreshing sleep,One of the symptoms: cognitive impairment or orthostatic intolerance.

2) Age 20–60 years, of either sex, and right-handed.3) No use within the past month of treatments considered likely to affect the primary outcomes or mechanistic assessments, including herbal formulas, acupuncture, other related non-pharmacological therapies, and antibiotics, probiotics, or prebiotics.4) Able to communicate and complete study questionnaires, and willing to accept randomization and provide written informed consent.

Exclusion criteria:

Fatigue symptoms that do not lead to a substantial reduction in the capacity for work, education, social and recreational activities, or activities of daily living.Severe comorbid conditions, including decompensated cardiac, cerebrovascular, hepatic or renal disease, malignancy, active infection, or neurological disorders.Severe psychiatric disorder, or severe depressive symptoms requiring immediate treatment, as indicated by a Self-Rating Depression Scale score ≥63 or clinical judgment.Pregnancy, planned pregnancy or lactation.Contraindications to MRI, such as pacemaker, neurostimulator, metallic implants or insulin pumps, in participants enrolled in the imaging substudy.Morbid obesity, defined as BMI > 45 kg/m^2^.Any other condition that, in the opinion of the investigator, would contraindicate participation or continuation in the trial, or would provide a more likely alternative clinical explanation for fatigue.

### Sample size calculation

3.4

The sample size was determined for the primary outcome, defined as the between-group difference in change in Fatigue Scale-14 (FS-14) score from baseline to week 8. Based on pilot data, the expected mean difference between groups was 1.60 points, with a pooled SD of 3.28. Using a two-sided alpha of 0.05 and 80% power for a superiority design, the required sample size was 66 participants per group. Assuming a 20% dropout rate, the final target sample size was set at 83 participants in each group, giving a total of 166 participants. The calculation was based on the standard formula for comparing two parallel groups and confirmed using G*Power (v3.1) and R (v4.3.3).

### Randomization and blinding

3.5

Randomization will be performed using block randomization with randomly varying block sizes of 4 and 6. The allocation sequence will be generated independently by a statistician using R (version 4.3.3). To maintain balance across the two participating sites, randomization will be stratified by study center. Sequentially numbered, sealed, opaque envelopes containing the group assignments will be prepared in advance and kept by an independent trial coordinator. After eligibility has been confirmed and baseline assessments completed, the coordinator will open the next envelope in sequence to reveal the allocation. The allocation sequence will be centrally generated and maintained by an independent coordinator not involved in recruitment. Because Tuina is delivered as a manual intervention, neither therapists nor participants can be blinded to treatment assignment. However, outcome assessors, laboratory personnel, imaging analysts, data managers, and statisticians will remain masked to group allocation wherever applicable. Unblinding will occur only after database lock or when required for safety reasons. Although baseline fatigue severity is clinically important, it was not included as a stratification factor in the final randomization scheme in order to maintain consistency of the allocation procedure throughout participant enrollment.

Questionnaire-based outcomes will be collected by assessors who are not involved in treatment delivery and who will remain unaware of group allocation. Biological samples will be labeled with coded study identifiers before laboratory processing, and laboratory personnel performing metabolomic and microbiome analyses will remain blinded to treatment assignment. Imaging data will be de-identified and coded before preprocessing and analysis, and imaging analysts will work with masked group labels until completion of the predefined preprocessing and analytic steps. Final statistical analyses will be conducted using masked group labels, with unblinding only after database lock unless required for participant safety or other prespecified operational reasons.

### Interventions

3.6

#### Experimental group

3.6.1

Participants in the experimental group will receive the Tuina intervention in addition to the general trial advice provided to all participants, including maintaining their usual activity level and refraining from initiating any new CFS-related therapies during the 8-week treatment period. The Tuina intervention will be delivered twice weekly for 8 weeks (16 sessions in total), with a minimum interval of 48 h between sessions. Each session will last approximately 20 min. Any concomitant treatments and changes in medical care during the study period will be recorded in the case report forms (CRFs).

The Tuina therapy will focus on the abdomen (Conception vessel and key abdominal acupoints), back (the first line of the Bladder meridian and Back-Shu points), and lumbar region, with the aim of influencing autonomic regulation and gastrointestinal function. The intervention will be delivered by six licensed Tuina therapists, each with at least 5 years of clinical experience. Before participant enrollment, all therapists will receive unified training in the study-specific standard operating procedures.

A typical 20-min treatment session will follow a standardized sequence. In the supine position, one-finger pushing will be applied to Zhongwan (CV12), Qihai (CV6), and Tianshu (ST25) for 1 min at each point, followed by palm rubbing over the abdomen for 5 min until local warmth is achieved. Kneading will then be performed at CV12, CV6, and ST25 for 1 min at each point, followed by pressing-kneading at Zusanli (ST36) and Sanyinjiao (SP6) for 1 min at each point. In the prone position, one-finger pushing and rolling will be applied along the first line of the Bladder meridian on the back, with emphasis on the Back-Shu points of the five zang organs, including Feishu (BL13), Xinshu (BL15), Ganshu (BL18), Pishu (BL20), and Shenshu (BL23). Linear rubbing will then be performed along the Governor vessel and Bladder meridian until local warmth is achieved. Acupoints will be located in accordance with GB/T 12346–2021 (Naming and Positioning of Acupoints). Representative images of the standardized Tuina procedures are provided in Supplementary Figure 1. Detailed acupoint information and intervention procedures are provided in Supplementary Table 1.

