#### Control group

3.6.2

The control group will receive standardized usual care. Participants in the control group will receive health education and symptom-oriented management once weekly for 8 weeks, with each session lasting approximately 40 min. The program will cover balanced diet, sleep hygiene, stress management, psychological support, and tailored symptom management advice when clinically indicated. To reduce contamination, additional interventions specifically targeting fatigue, such as newly initiated pharmacotherapy, acupuncture, or herbal prescriptions, will not be permitted during the 8-week treatment period unless deemed clinically necessary. Stable pre-existing medications may be continued. Standardized usual care will be delivered by two TCM attending physicians who are licensed clinicians and have completed study-specific training and Good Clinical Practice certification. Concomitant medications and any rescue treatments will be recorded at each visit. Staff qualifications, training records, and adherence to the intervention protocol will be documented and audited.

Participant blinding is not feasible because of the nature of the Tuina intervention. The control group will receive health education and symptom-oriented management with standardized contact procedures and approximately matched total contact time, which is intended to help reduce imbalances in attention and trial engagement between groups. However, because treatment frequency and tactile contact cannot be matched, residual differences in treatment expectancy and performance effects may remain. This comparator was chosen to reflect current clinical management for CFS, in which symptom-oriented and supportive care remains the predominant non-pharmacological management approach. The study therefore evaluates standardized Tuina in comparison with standardized usual care, rather than against an inert, no-treatment, or fully attention-matched sham condition.

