### Statistical analysis

3.9

Statistical analyses will be performed using SPSS version 26.0 (IBM Corp., Armonk, NY, USA). Baseline characteristics will be summarized as mean (SD) or median (IQR) for continuous variables and as number (%) for categorical variables, as appropriate. Longitudinal outcomes will be analyzed using linear mixed-effects models including fixed effects for group, time, and group-by-time interaction. The models will be adjusted for baseline outcome values, study center, and sex, with additional prespecified covariates included where appropriate. For the primary outcome analysis, baseline FS-14 score will be included as a covariate. Secondary clinical outcomes will be interpreted with consideration of multiplicity, and exploratory omics and imaging analyses will be interpreted as hypothesis-generating. All tests will be two-sided, and a *p* value <0.05 will be considered statistically significant. The primary efficacy analysis will follow the intention-to-treat principle. A per-protocol analysis will be conducted as a sensitivity analysis. The primary comparison will be the between-group difference in change in FS-14 total score from baseline to week 8, estimated from the mixed-effects model. Missing data will be handled under the missing-at-random assumption inherent to mixed-effects models, and additional sensitivity analyses will be conducted if warranted. Because this is a multicenter trial, study center will be included in the analysis model to account for potential between-center variability. All statistical analyses will be performed with group allocation concealed until database lock. The full trial protocol is provided in this article and its online Supplementary materials.

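### The sample size and the listed model terms make no allowance for clustering by provider, so if outcomes cluster the 80% power is optimistic and the standard error too small

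*Protocol article*

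**What the plan says.** On delivery, section 3.6.1 of the protocol article says "The intervention will be delivered by six licensed Tuina therapists, each with at least 5 years of clinical experience", and section 3.6.2 says "Standardized usual care will be delivered by two TCM attending physicians". Each provider is described as working in one arm only, so providers are nested within arm.

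On size, section 3.4 says "the expected mean difference between groups was 1.60 points, with a pooled SD of 3.28" and "Using a two-sided alpha of 0.05 and 80% power for a superiority design, the required sample size was 66 participants per group". It adds "Assuming a 20% dropout rate, the final target sample size was set at 83 participants in each group" and "The calculation was based on the standard formula for comparing two parallel groups". It mentions no ICC, design effect or provider.

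On analysis, section 3.9 names a linear mixed-effects model with group, time and their interaction, and says "The models will be adjusted for baseline outcome values, study center, and sex". It leaves room for further prespecified covariates without naming them. Center is the only source of between-cluster variability that it addresses.

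**The concern.** Tuina is a hands-on treatment of 16 sessions, and usual care is eight sessions of about 40 minutes that include psychological support and tailored advice. In both arms the result may depend on who delivers it. Participants who share a provider may then have correlated outcomes. Randomization does not remove this correlation, because it arises after allocation.

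A center main effect shifts both arms equally, whereas each provider treats only one arm. It therefore cannot absorb differences between therapists within the Tuina arm. If there were one physician per hospital (the split is not stated), the difference between the two physicians would act as a center-by-group effect, which the listed terms do not include.

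Two things are at stake. The confidence interval for the Tuina effect could be too narrow, so that a few strong therapists are read as an effect of Tuina in general. The trial is also planned at exactly 80% power, with no stated margin for such a loss.

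**Working it through.** **Inputs from the article.** Difference 1.60, SD 3.28, two-sided alpha 0.05, power 80%, 66 per arm, 20% dropout, 83 per arm (section 3.4); 1:1 allocation (section 3.1); six therapists (3.6.1); two physicians (3.6.2).

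**Assumptions, not in the article.** ICC from 0 to 0.05, equal caseloads, one provider per participant.

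**The plan's own figure.** n = 2 × (3.28/1.60)² × (1.960 + 0.842)² = 65.97, so 66 per arm. 66/0.8 = 82.5, so 83 per arm and 166 in total. The stated figures reproduce under independence. The standard error is 3.28 × √(2/66) = 0.571, and 1.60/0.571 = 2.80.

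**Adding clustering.**
- Completers per provider: 66/6 = 11 (Tuina), 66/2 = 33 (control).
- Design effect in an arm: 1 + (m − 1) × ICC.
- Variance factor f: the mean of the two arms' design effects.
- Power = Φ(2.80/√f − 1.96).
- Type I error of a model that ignores providers = 2 × [1 − Φ(1.96/√f)].

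Clustering in the Tuina arm only:

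| ICC | Tuina design effect | f | SE ratio √f | Power | Type I error |
|---|---|---|---|---|---|
| 0 | 1.00 | 1.000 | 1.00 | 80% | 5.0% |
| 0.01 | 1.10 | 1.050 | 1.02 | 78% | 5.6% |
| 0.02 | 1.20 | 1.100 | 1.05 | 76% | 6.2% |
| 0.05 | 1.50 | 1.250 | 1.12 | 71% | 8.0% |

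The same ICC in both arms: at 0.01 the control design effect is 1.32, f = 1.21, power 72% and type I error 7.5%. At 0.02, f = 1.42, with 65% and 10%. At 0.05, f = 2.05, with 50% and 17%. These rest on a normal approximation with two control clusters (about 1 degree of freedom), so they show direction more than size.

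**Offset from baseline adjustment.** Let r be the correlation of baseline with week-8 FS-14 (assumed; 3.28 read as the SD of the score), with the therapist variance unchanged. In the Tuina-only case f becomes (1 − r²) + 5 × ICC. For r = 0.5, ICC 0.02 gives 0.75 + 0.10 = 0.85 and 86% power; ICC 0.05 gives 0.75 + 0.25 = 1.00 and 80%. At ICC 0.05, r = 0.3 gives f = 1.16 and 74%; r = 0.7 gives f = 0.76 and 90%.

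**What a therapist random effect can deliver.** With six therapists of 11 completers, the chance that the therapist variance is estimated at zero is P[F(5, 60) ≤ 1/(1 + 11 × ICC/(1 − ICC))]. This is 51%, 46% and 32% at ICC 0.01, 0.02 and 0.05. Simulating the partially nested test with small-sample degrees of freedom gives about 73% power at ICC 0 and about 63 to 64% at ICC 0.05, where the interval is on average about 22% wider than that of the model without the therapist effect.

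**The case against.** The strongest objection is that the consequence is conditional. It needs an ICC above zero and participants who stay largely with one provider, and the article gives neither. It does not say that one therapist delivers all 16 sessions, and section 3.12 allows flexible scheduling. Rotation would dilute clustering in the Tuina arm. Unified training, a standardized sequence and adherence checks should also reduce differences between therapists. This stands, and the point has to be worded conditionally. These measures may lower the ICC, but they are not a statistical adjustment.

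Second, section 3.9 describes no random effects at all, and that structure may sit in supplementary material or an analysis plan not shown here. This also stands. The sample-size part, where a completed calculation assumes independence, is firmer than the model part.

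Third, section 3.4 takes no explicit credit for adjusting for baseline FS-14, which could recover some or all of the lost power. That is correct for power. It does not repair the type I error: the therapist variance stays while the residual variance shrinks.

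A reader might infer that the standard error is wrong as a matter of fact, or that the trial really has 50% power and a 17% false-positive rate. The article does not support this. Those two figures need both arms to cluster at the same assumed ICC of 0.05, estimated from two control physicians.

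**Conclusion.** The point holds in conditional form. Section 3.4 assumes independent participants, the terms listed in 3.9 include no provider, and the center effect does not fill that gap.

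If outcomes cluster and participants keep mainly one provider, the plan understates the standard error. With Tuina-arm clustering alone and ICC 0.01 to 0.05, the factor is about 1.02 to 1.12, power is about 78% to 71% before any gain from baseline adjustment, and the type I error is about 5.6% to 8%. At ICC 0 nothing changes. Clustering in the control arm would worsen the figures by an amount that two physicians cannot reliably reveal.

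This supports a sensitivity analysis and an honest power statement. It does not show that the planned primary analysis is invalid, and given the power cost under six therapists it does not settle that the therapist model should become primary.

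**What to change.** 1. Record the provider at every session in both arms. Section 3.12 lists session completion, adherence and variations as the content of treatment records but does not mention provider identity, which is hard to reconstruct later.
2. In 3.9, prespecify a sensitivity analysis of the primary FS-14 comparison with a therapist random effect in the Tuina arm only (partially nested model, small-sample degrees of freedom). Classify each participant by the provider of most sessions.
3. In 3.4, restate power over an assumed ICC of 0 to 0.05 at the planned 166, without adding participants.
4. State as a limitation that the effect of the two control physicians cannot be separated from that of the control programme.

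The cost is one field in the session record and a few lines of text. The sensitivity analysis will be imprecise: with six therapists the variance is estimated at zero about a third to a half of the time at ICC 0.01 to 0.05, and the interval is on average roughly 10 to 20% wider. A zero estimate should therefore not be reported as evidence that therapists do not differ.
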